### Participant Timeline

Follow-up will be carried out from the beginning of the randomization until the participant is discharged. The variables will be collected in the operating room postoperatively; variable collection will occur at a higher frequency within the first 48 hours.

The research team will monitor the possible adverse events, including the time of occurrence, duration, intensity, course, and outcome, in order to make an assessment of the causal relationship between the adverse event and the drug.

### Statistical Analyses

#### Sample Size Calculation

The literature reviewed reflects a need for postoperative inotropic vasoactive support ranging from 35% to 40%. In the sample size calculation, we propose that better myocardial protection will be reflected in a lower need for electrical cardioversion, lower pharmacological inotropic or mechanical support, and a lower incidence of myocardial infarction.

For a hypothetical reduction of inotropic support within the first 24 postoperative hours from 38% to 25%, with an α risk of 5%, at a statistical power of 80% (β=.20), by bilateral test with application of the Fleiss correction factor, and estimating losses of 10%, 474 participants distributed into two groups will be necessary.

Participants will be assigned to groups by simple randomization of the sample, obtaining a computer sequence by Stata 16 (StataCorp). The computer distribution will assign 234 participants to the intervention group (DNS) and 240 participants to the control group (blood cardioplegia). When patients arrive at the theater, perfusionists will enroll participants.

#### Analyses

A description of the data from each group of the study and the total sample will be carried out. The properties of the original variables will be defined, and the aforementioned composite variables will be created. The main variable—*prolonged low cardiac output syndrome*—will be created from the following original variables: *presence of two or more inotropic agents at 24 hours of admission*, *mechanical support with IABC*, and/or *mechanical support with ECMO or other ventricular assistance*. The main composite variable—*acute cardiovascular event*—will be created from the following variables: *perioperative myocardial infarction*, *prolonged low cardiac output syndrome*, *prolonged vasoplegia*, and/or *VT or VF episodes in the first 24 hours*.

The quantitative variables shall be described through the mean (SD), median (IQR), 95% CI, and minimum and maximum values. Qualitative variables shall be presented as relative and absolute frequencies. To ensure the uniformity of the groups, a detailed analysis will be made by evaluating the association using the Pearson correlation coefficient and the *P* value by means of the Student-Fisher *t* test; correction for unequal variances for the quantitative variables, and the association with the odds ratio and the *P* value, will be obtained with chi-square tests for the categorical variables.

The raw effect of each type of cardioplegia on the acute cardiovascular event will be estimated using a logistic regression model.

Two populations will be defined through intention-to-treat analysis and by biological efficacy. The first population will include all the initially randomized subjects, including all those who leave the study due to noncompliance. The second population will include all those subjects who complete the study within the same group in which they were randomized. An intermediate safety analysis will be performed when approximately 50% of patients have been randomized.

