### Outcome Measures

The main variables of the study will be the composite clinical variable *acute cardiovascular event* and the biochemical variable *maximum postoperative troponin value*.

The *acute cardiovascular event* variable will consist of one or several of the following events:

Early perioperative myocardial infarction: occurring during the first 72 hours after surgery and defined according to the criteria of the Task Force of the European Society of Cardiology, the American Heart Association, and the World Heart Federation.Prolonged low cardiac output: defined as the need to maintain support with two or more inotropic and/or other circulatory mechanical assistance devices—intra-aortic balloon counterpulsation (IABC) or extracorporeal membrane oxygenation (ECMO)—beyond the first 24 postoperative hours.Appearance of ventricular arrhythmias: ventricular tachycardia (VT) and ventricular fibrillation (VF) requiring electrical cardioversion in the first 24 postoperative hours.

To analyze the effect of cardioplegia on myocardial protection at a biochemical level, the level of troponins will be monitored upon arrival at the ICU and during the first 48 hours. Likewise, the maximum troponin peak will be collected during the first 48 postoperative hours.

Other secondary variables of efficacy and safety will be analyzed. Among the intraoperative variables, surgical times (ie, ischemia time and cardiopulmonary bypass times), the volume of cardioplegia solution administered and its route of administration, temperature, average blood pressure, and maximum blood glucose values, as well as the need for electrical cardioversion after aortic cross-clamp release, will be monitored.

Among the postoperative variables, the occurrence of atrial fibrillation will be registered, as well as the requirement for inotropic and mechanical pharmacological support, time to withdrawal, and the occurrence of clinical complications (ie, deterioration of ventricular function upon hospital discharge, surgical reintervention, prolonged mechanical ventilation, acute kidney injury, infectious complications, convulsive activity, or stroke). The need for ICU readmission, ICU and hospital length of stay, and mortality will also be noted.

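### The primary composite has three components in Outcome Measures but four in Analyses, and the added one, prolonged vasoplegia, is undefined

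*Protocol article*

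**What the plan says.** Outcome Measures in the protocol article names two main variables, the composite acute cardiovascular event and the maximum postoperative troponin. It says the composite "will consist of one or several of the following events" and lists three:

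- myocardial infarction in the first 72 hours after surgery;
- prolonged low cardiac output, meaning at least two inotropes and/or a mechanical device (IABC or ECMO) still needed after the first 24 postoperative hours;
- "ventricular tachycardia (VT) and ventricular fibrillation (VF) requiring electrical cardioversion in the first 24 postoperative hours".

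The Analyses section announces that "the aforementioned composite variables will be created", so it presents itself as deriving the same variable. Its list has four items: perioperative infarction, prolonged low cardiac output syndrome, "prolonged vasoplegia", and "VT or VF episodes in the first 24 hours". It derives low cardiac output from "presence of two or more inotropic agents at 24 hours of admission" together with fields for IABC and for ECMO or other ventricular assistance. The device fields carry no time condition. The composite is then the outcome of the planned logistic regression.

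**The concern.** A primary endpoint needs one rule that classifies each patient as event or non-event. Here two rules are printed for the same variable, and a patient whose only complication is vasoplegia is an event under one and not under the other. The fourth component also has no criteria: no threshold, no duration that would make it prolonged, no time window. Using the Analyses version would therefore need a second decision that the article does not make.

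Both decisions can still be taken once results by arm are known. The event count, the odds ratio and possibly the significance of the primary clinical comparison would then rest on a choice that was not fixed in advance.

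**Working it through.** **Side by side**

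| Element | Outcome Measures | Analyses |
|---|---|---|
| Myocardial infarction | first 72 h | perioperative, window not repeated |
| Inotropes | two or more, maintained beyond 24 h | two or more, at 24 h of admission |
| Mechanical devices | maintained beyond 24 h | no time condition stated |
| VT/VF, first 24 h | only if electrically cardioverted | episodes, no cardioversion condition |
| Vasoplegia | absent | included, undefined |

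The rows differ in strength. The vasoplegia row is a contradiction, because a whole component cannot be an abbreviation of something absent from the other list. The device and VT/VF rows are omissions of a qualifier. Taken literally, a balloon removed at 10 hours or a VT run that ends by itself is an event under Analyses and not under Outcome Measures. The infarction and inotrope rows are close enough to be the same rule in shorter words.

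**Does the sample size show which version is meant?** Inputs from Sample Size Calculation: 38% versus 25%, two-sided α 5%, power 80%, Fleiss correction, 10% losses.

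- Uncorrected: n₀ = [1.96·√(2·0.315·0.685) + 0.842·√(0.38·0.62 + 0.25·0.75)]² / 0.13² = 199.2 per arm.
- Corrected: n = (n₀/4)·[1 + √(1 + 4/(n₀·0.13))]² = 214.4, so 215 per arm.
- Losses: 215 × 1.10 = 236.5, so 237 per arm and 474 in total, as stated. Dividing by 0.90 instead gives 239 per arm, 478 in total.

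The figure reproduces, but 38% and 25% are rates of inotropic support within 24 hours. That is neither version of the composite, so the calculation does not identify the intended one. The rationale in the same section is more informative: it expects better protection to show in cardioversion, inotropic or mechanical support, and infarction. Those are the three components of Outcome Measures, without vasoplegia.

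**Illustration of what is at stake.** The article gives no rate for the composite or for vasoplegia, so the rates below are assumptions.

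- Evaluable patients: control 240 × 0.9 = 216; del Nido 234 × 0.9 = 210.6; r = 210.6/216 = 0.975.
- Three-component rates: control p₁; del Nido p₂ = p₁ × 25/38, the planned relative reduction.
- Adding independent vasoplegia at rate v: p′ = 1 − (1 − p)(1 − v) in each arm.
- Power, with d = p₁ − p₂, pooled rate p̄ and effective size n′ = 216·[1 − (r+1)/(2·r·d·216)]²: Φ{[d·√(r·n′) − 1.96·√((r+1)·p̄(1−p̄))] / √(r·p₁(1−p₁) + p₂(1−p₂))}.

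Worked case, p₁ = 15%: p₂ = 9.87%, d = 0.0513, n′ = 178.3, z = −0.505, power 31%, odds ratio 0.62. With v = 5%: 19.25% versus 14.38%, odds ratio 0.70, power 23%.

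Power when vasoplegia is unaffected by treatment:

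| Control rate, three components | Without vasoplegia | v = 5% | v = 10% | v = 15% |
|---|---|---|---|---|
| 10% | 20% | 13% | 11% | 9% |
| 15% | 31% | 23% | 18% | 15% |
| 20% | 42% | 34% | 27% | 23% |
| 38% | 80% | 73% | 67% | 60% |

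In the 15% row the odds ratio moves from 0.62 to 0.70, 0.76 and 0.80.

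If vasoplegia instead falls by the same proportion (del Nido rate v × 25/38), power at the 15% control rate rises from 31% to 39%, 47% and 55%, with the odds ratio between 0.60 and 0.62. So the direction depends on an assumption that the article does not settle.

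**The case against.** The best defence is that Analyses refers back to the composite already defined, and that its items read like database field names. On that reading "VT or VF episodes in the first 24 hours" and the IABC and ECMO fields are short labels for the fuller definitions. The device fields also feed a variable still called prolonged, which Outcome Measures ties to more than 24 hours. This defence is fair for those two differences. A reader might infer that Analyses counts device support at any time, or that the sections conflict on three equal counts. The text does not support that: no such phrase appears, and only vasoplegia is a proven conflict. The inotrope timing is weaker still, since presence at 24 hours is an ordinary way to record support maintained to that point. The defence does not reach vasoplegia.

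The sample-size rationale leans towards the three-component version, so the choice is less open than if the article were silent. It does not formally override the Analyses text.

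A reader might also infer that the four-component version dilutes the treatment effect. That holds only if the added events do not respond to cardioplegia, which the article nowhere states; the last calculation shows the opposite result under another assumption. The low starting power in some rows comes from the assumed event rate, not from this inconsistency. Finally, one might suppose that all the data needed are already collected. Withdrawal times for inotropic and mechanical support are planned, but vasoplegia is not among the listed variables and has no recording criteria.

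This is not a matter that can be left to an unseen analysis plan: the article states both definitions, and they disagree.

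**Conclusion.** The concern stands for vasoplegia: the primary composite has three components in one section and four in another, the fourth is undefined, and no text says which governs. The missing cardioversion and device-timing conditions are ambiguities to be aligned, not proven contradictions. The conclusion rests on the wording alone and needs no assumed rate.

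Neither the size nor the direction of the effect can be derived from the article. Under the stated assumptions (independent vasoplegia at 5% to 15%, unaffected by treatment), power falls by 8 to 16 percentage points at a 15% control rate and by 7 to 20 at 38%; with a proportional treatment effect on vasoplegia it rises. Either way, the primary clinical result can depend on which section is followed, so this must be fixed before analysis.

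**What to change.** Before unblinding, state one definition of the acute cardiovascular event in both sections. The three-component version in Outcome Measures is the natural choice, because it matches the sample-size rationale. In Analyses:

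- remove vasoplegia from the primary composite;
- attach the electrical-cardioversion condition to VT/VF;
- attach the beyond-24-hours condition to IABC, ECMO and other devices, and use the same time origin for inotropes;
- repeat the 72-hour window for infarction.

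If vasoplegia is being recorded, give it a definition and a time window, and report it separately or in a sensitivity analysis of the four-component version.

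For the primary composite the cost is a wording change. For vasoplegia it may be more: if it was not recorded prospectively against set criteria, a separate report could need retrospective data. Correcting the primary endpoint does not depend on that.

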Subgroup analyses will be carried out in four populations: elderly patients (over 80 years), patients undergoing prolonged cardiopulmonary bypass (longer than 120 minutes), patients with low ventricular ejection fraction (less than 30%), and patients subjected to coronary artery bypass grafting.

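### The only stated effect model for the composite is unadjusted, after unstratified randomisation, with baseline P values relied on for balance: valid, but an avoidable loss of precision

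*Protocol article*

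**What the plan says.** Three statements in the protocol article bear on this.

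- **Allocation** (Sample Size Calculation): "Participants will be assigned to groups by simple randomization of the sample". No stratification factor is named. The arm sizes are given as 234 (del Nido) and 240 (blood cardioplegia).
- **Effect model** (Analyses): "The raw effect of each type of cardioplegia on the acute cardiovascular event will be estimated using a logistic regression model". No covariate is named and no other effect model is given. Maximum troponin, the second main variable, has no stated model.
- **Baseline comparison** (Analyses): "To ensure the uniformity of the groups, a detailed analysis will be made by evaluating the association using the Pearson correlation coefficient", followed by t-test and chi-square P values.

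Outcome Measures plans subgroups by age over 80, LVEF under 30%, coronary artery bypass grafting (CABG) and bypass time over 120 minutes. The Discussion describes elderly patients and those with low ejection fraction as high-risk.

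**The concern.** Eligibility covers nearly all elective adult bypass surgery, so baseline risk should vary widely. The article itself singles out age, ventricular function and CABG as worth separate study, yet none of them enters the randomisation or the stated model. When strong predictors are left out of both, their variation stays in the comparison as noise and some power is lost.

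The baseline tests do not fill the gap. Under randomisation any baseline difference is due to chance, so each P value tests a null hypothesis already known to be true. A test can miss a gap in a strong predictor and flag one in an irrelevant variable. The Strengths and Limitations section relies on collecting other myocardial protection variables to address bias. Those listed in Outcome Measures are recorded during or after surgery and cannot correct a baseline imbalance.

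**Working it through.** **1. The plan's own figure.** Inputs from Sample Size Calculation: 38% against 25%, two-sided 5%, 80% power, Fleiss correction, 10% losses.

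- Uncorrected n per arm = [1.96·√(2·0.315·0.685) + 0.8416·√(0.38·0.62 + 0.25·0.75)]² / 0.13² = 199.2.
- Fleiss correction: (199.2/4)·[1 + √(1 + 4/(199.2·0.13))]² = 214.4, so 215 per arm, 430 in total.
- Losses: 215 × 1.10 = 236.5, so 237 per arm and 474 in total, as stated. Dividing instead, 430/0.90 gives 478, which is 0.8% away.

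**2. Power with and without adjustment.** The inputs were marginal rates of 38% and 25%, the 234:240 split, and 474 patients or 427 (474 × 0.90). Each trial had one normally distributed baseline risk score, and logistic Wald tests were run with and without it. There were 3,000 simulated trials per setting, so each power figure has a Monte Carlo standard error of about 0.7 points. The strength of the score is my assumption, because the article gives none.

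| Score, log-OR per SD (AUC) | N=474: raw → adjusted | N=427: raw → adjusted | Conditional OR |
|---|---|---|---|
| 0.4 (0.61) | 86.9% → 87.5% | 81.7% → 83.1% | 0.53 |
| 0.7 (0.68) | 86.7% → 89.7% | 82.5% → 85.2% | 0.51 |
| 1.0 (0.74) | 86.4% → 91.5% | 83.1% → 88.4% | 0.49 |
| 1.3 (0.79) | 86.4% → 93.2% | 82.8% → 90.8% | 0.45 |

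The gain is 0.6 to 6.8 points at N=474 and 1.4 to 8.0 points at N=427. Type I error under the null lay between 0.043 and 0.055 for both models. Raw power exceeds 80% because the Wald test carries no continuity correction and, at 474, because the loss allowance is still included.

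The marginal odds ratio at the planning rates is (0.25/0.75)/(0.38/0.62) = 0.54. The adjusted model targets a different quantity, shown in the last column.

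**3. Size of chance imbalance.** The 95% limit for a between-arm gap in a factor of prevalence q is 1.96·√[q(1−q)(1/234 + 1/240)]. The prevalences are assumed.

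- q = 10%: ±5.4 points
- q = 30%: ±8.25 points
- q = 50%: ±9.0 points

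A gap above 10 points has probability 0.03% at q = 10% and 3% at q = 50%. As an illustration, take a factor with 10% prevalence that adds 30 points of risk, at its 95% limit. It moves the risk difference by 0.054 × 30 = 1.6 points, against a planned effect of 13.

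**The case against.** The strongest reply is that nothing here is an error. An unadjusted comparison after randomisation is unbiased, keeps its 5% level, matches the two-proportion calculation behind the sample size, and has more than 80% power at the planning rates. Covariate lists usually sit in a full protocol or SAP, neither of which is shown, and naming a raw estimate does not exclude an adjusted one. If the covariates are weak, the gain is about one point. All of this stands, and it limits the point to efficiency.

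Several stronger readings are tempting, but the documents do not support them.

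- **That chance imbalance will bias the result.** It is random error, already covered by the raw confidence interval, and large gaps are unlikely with 474 patients.
- **That precision is given up for nothing.** Adjustment changes the odds ratio from marginal to conditional. Recruitment also began in 2018, with analysis expected in autumn 2020 and a safety analysis at about half of randomisation, so a late change needs care.
- **That the P values will select covariates.** The article does not say so.
- **That the troponin analysis loses a known amount.** No troponin model is stated, so there is nothing to measure a loss against.

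The reply does not rescue the baseline tests. Their stated purpose is one that such tests cannot serve, and leaving detail to another document does not change that.

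**Conclusion.** The point holds as an avoidable loss of precision in the stated analysis of the composite, together with a baseline testing procedure that cannot do what is asked of it. Neither invalidates the trial.

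The range of roughly 1 to 8 power points rests on two assumptions: a baseline score with AUC between 0.61 and 0.79, and event rates of 38% and 25%. Those rates describe inotropic support. The article gives no rate for the composite, and the gain there could differ.

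**What to change.** Before anyone compares outcomes by arm:

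- Prespecify as the main model a logistic regression of the composite on arm, age, LVEF and surgery type (CABG or not, isolated or combined). All are known before surgery.
- Report a standardised (marginal) risk difference beside the adjusted odds ratio, and keep the raw estimate as a sensitivity analysis.
- Analyse maximum troponin on the log scale by linear regression with the same covariates.
- Do not adjust for bypass or ischaemia time. Both arise after randomisation, and the Introduction cites a meta-analysis in which cross-clamp and bypass times were shorter with del Nido, so they may be affected by treatment.
- Replace the baseline significance tests with a descriptive table by arm.

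No extra patients are needed, and the analysis work is small. At the planning rates 427 patients would give about 135 events (0.25 × 211 + 0.38 × 216) for five coefficients; a rarer composite would give fewer. There are two real costs. The change of main model must be documented and made without sight of results by arm. And readers will see a conditional odds ratio that differs from the raw one unless the standardised effect is reported with it.

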### Monitoring and Quality Assurance

The clinical trial is defined as a *low intervention–level trial*, due to the fact that the cardioplegia solutions used are already approved and used in accordance with the terms of the marketing authorization; as well, the solutions are extensively backed up by published scientific evidence on their safety and efficacy (Royal Decree 1090/2015).

The confidentiality of the identity of the volunteers will be respected if the data obtained in this study are published. Subjects’ data included in the study will be treated in accordance with Organic Law 15/1999, December 13, on the Protection of Personal Data.

### Ethics Approval and Consent to Participate

This study has been registered in the European Union Drug Regulating Authorities Clinical Trials Database (EudraCT) (No. 2017-005144-14) and at ClinicalTrials.gov (No. NCT04094168). The study protocol has been approved by the Ethics Committee of Puerta de Hierro Majadahonda University Hospital and was approved by the Spanish Medicines and Health Products Agency (AEMPS).

This clinical trial will be carried out under conditions of respect for the fundamental rights of the person and the ethical principles that affect biomedical research with human beings, as well as in accordance with international recommendations contained in the Declaration of Helsinki and its subsequent revisions. Likewise, national recommendations will be followed in accordance with the guidelines of the AEMPS.

Participants will receive information, both orally and in writing, regarding the manner in which the study will be carried out, the study aims, possible risks that may arise from the study, and the rules that must be observed during the follow-up period. If the patient fulfils the inclusion criteria and agrees to participate in the study, she or he will provide written informed consent; providing consent will not prevent the patient from withdrawing such consent and abandoning the study at any time and for any reason.

